**Methods:**

An evaluator-blinded RCT will be conducted in 42 children aged between 6 and 12 years. Before randomization, children will be stratified according to their House Functional Classification Scale, age and type of corticospinal tract wiring. A 2-week day-camp will be set up in which children receive intensive mCIMT therapy for 6 hours a day on 9 out of 11 consecutive days (54 h) including AOT or control condition (15 h). During AOT, these children watch video sequences showing goal-directed actions and subsequently execute the observed actions with the more impaired UL. The control group performs the same actions after watching computer games without human motion. The primary outcome measure will be the Assisting Hand Assessment. Secondary outcomes comprise clinical assessments across body function, activity and participation level of the International Classification of Function, Disability and Health. Furthermore, to quantitatively evaluate UL movement patterns, a three-dimensional motion analysis will be conducted. UL function will be assessed at baseline, immediately before and after intervention and at 6 months follow up. Brain imaging comprising structural and functional connectivity measures as well as Transcranial Magnetic Stimulation (TMS) to evaluate corticospinal tract wiring will be acquired before the intervention.

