### Hypothesis

The RCT will address the following research hypotheses:mCIMT, in combination with AOT, augments the treatment effects immediately after intervention and results in improved UL function with longer retention beyond mCIMT alone.The combination of neurological predictors, i.e. neuroanatomical brain lesion characteristics, structural and functional connectivity and CST wiring pattern, better determines treatment response compared to clinical predictors.Children with a bilateral and ipsilateral CST wiring respond less to the treatment compared to children with contralateral CST wiring in both intervention groups.In children with more lesions or disturbed connectivity in the areas involving the mirror neuron system, AOT is not as effective as in those with less lesions in this area.

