### Sample size

Sample size estimate is based on the primary endpoint, which is defined as the immediate effect of the intervention on the primary outcome measure, i.e. bimanual performance measured with the Assisting Hand Assessment (AHA). The smallest detectable difference has been reported to be 5 AHA units [24]. A previous intervention study of intensive therapy in children with uCP [6], reported a standard deviation of 5.5 AHA units, which would translate into an effect size of 0.9. With this effect size, an alpha-level of 0.05, and a statistical power of 0.80, a sample size of 21 children is needed in each group to detect a difference equal to or larger than the smallest detectable difference of 5 AHA units between groups [24, 25]. Sample size estimates were calculated with G*Power [26, 27].

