### Statistical analysis

Descriptive statistics of the outcome variables will be reported by using means and standard deviations or median and interquartile ranges, depending on their data distribution. Normality will be checked with the Shapiro-Wilk test and histograms will be checked for symmetry. Mixed models will be used to study changes after the intervention over time. By using random effects, these models are able to correct for the dependency among repeated observations. Furthermore, these models deal with missing data offering valid inferences, assuming that missing observations are unrelated to unobserved outcomes [70]. Based on the data distribution, linear (parametric) or generalized (non-parametric) linear mixed models will be used. Changes over time will be tested between groups, by analysing treatment-time interactions. In case of such a significant treatment-time interaction, changes over time will be investigated separately in each group. Significant time trends will be further investigated with pairwise post hoc tests to compare time points. Additionally, the effect size will be calculated using the Cohen’s d formula (small, 0.2–0.5; medium, 0.5–0.8, and large > 0.8) [71]. Both clinical (age, baseline AHA score, sensory function, mirror movements) and neurological predictors (brain lesion characteristics, structural and functional connectivity and CST wiring) will be included as covariates in the models for the primary outcome measure, together with their interaction with time and treatment to evaluate their potential confounding factor. The two-sided 5% level of significance will be used. All statistical analyses will be performed using SAS version 9.2 (SAS Institute, Inc., Cary, NC) and SPSS Statistics for Windows version 24.0 (IBM Corp. Armonk, NY: IBM Corp.).

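### Predictors with time and treatment interactions enter the primary AHA models without being separated from the confirmatory test, under a confounding rationale, and the second hypothesis gets no set-against-set comparison

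*Protocol article*

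**What the plan says.** The abstract sets the trial size: "An evaluator-blinded RCT will be conducted in 42 children aged between 6 and 12 years". The Sample size section derives it from a two-group comparison of the immediate AHA effect alone: "The smallest detectable difference has been reported to be 5 AHA units", an earlier study "reported a standard deviation of 5.5 AHA units", and with "an alpha-level of 0.05, and a statistical power of 0.80, a sample size of 21 children is needed in each group".

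The Statistical analysis section first describes mixed models in which the groups are compared through treatment-by-time interactions. It then says that four clinical predictors (age, baseline AHA, sensory function, mirror movements) and the neurological predictors (lesion characteristics, structural and functional connectivity, corticospinal tract (CST) wiring) will be covariates in the models for the primary outcome, "together with their interaction with time and treatment to evaluate their potential confounding factor". Testing follows one rule: "The two-sided 5% level of significance will be used".

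The second hypothesis in the Hypothesis section is that the combined neurological predictors "better determines treatment response compared to clinical predictors". The third and fourth concern CST wiring and lesions or connectivity in the mirror neuron system. The abstract's Discussion makes the role of neurological factors one of two main objectives.

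**The concern.** Three things are wrong with the covariate sentence as it stands.

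- **Primary model not identified.** The covariates and their interactions go into the models for the primary outcome, and nothing says which model carries the confirmatory AHA result. An adjusted or an unadjusted estimate could be presented as primary after the data are seen. If all terms enter together, the model is very large for 42 children.
- **Wrong purpose.** Treatment is randomised, so an imbalance in these factors is chance. They are prognostic factors or effect modifiers, which is how the second to fourth hypotheses treat them. Checking for confounding is not the task.
- **Second hypothesis not tested.** Covariate and interaction terms give a test for each predictor. The second hypothesis is about one set of predictors against another, and no such comparison is stated.

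At stake are the precision and traceability of the effect of adding action-observation training (AOT), the false-positive rate among predictors, and whether the second hypothesis can be confirmed or refuted.

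**Working it through.** **1. The plan's own figure.** Inputs from Sample size: difference 5, SD 5.5, alpha 0.05, "a statistical power of 0.80". The two-sided level is from Statistical analysis. Effect size = 5/5.5 = 0.909, given as 0.9. A two-sample t-test (noncentral t) with 21 per group has power 0.812 at 0.9 and 0.820 at 0.909; 20 per group falls just short of 0.80. The stated 21 per group is reproduced and is not in question. The standard error of the group difference is 5.5 × √(2/21) = 1.70 AHA units.

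**2. Leanest coding.** One number per domain, with three CST wiring types (Randomisation): age 1 + baseline AHA 1 + sensory 1 + mirror movements 1 + lesion 1 + structural 1 + functional 1 + CST 2 = 9 df. Lesion can be 1 df because the Structural MRI section gives a single global score (0–40).

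**3. Parameter count if all enter jointly.**
- T1-T2 change: intercept 1 + treatment 1 + predictors 9 + treatment interactions 9 = 20 coefficients for 42 children. That is 42/20 = 2.1 children per coefficient and 22 residual df.
- Four time points with three-way terms: 2 × 4 × (1 + 9) = 80 fixed effects on 42 × 4 = 168 correlated scores. With two-way terms only: 8 + 9 + 27 + 9 = 53.
- Saturation: 2 + 2P = 42 at P = 20.

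The article sets no limit on P. As an illustration, five sensory measures (four modalities plus monofilaments) and two diffusion metrics in the four tracts as printed (8 values before the two hemispheres are counted), with every other domain held at its minimum, give 1 + 1 + 5 + 1 + 1 + 8 + 1 + 2 = 20.

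**4. Power for 5 AHA units under joint entry.** Simulated T1-T2 change in 42 children, SD 5.5, independent centred predictors, each with a treatment interaction. How much variance the predictors explain is not in the article. Two assumptions are shown: none, or 30% carried by four predictors.

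| Predictor df | Pure noise | 30% of variance explained |
|---|---|---|
| 0 | 0.82 | – |
| 9 | 0.65 | 0.80 |
| 12 | 0.55 | 0.70 |
| 15 | 0.39 | 0.52 |
| 19 | 0.10 | 0.12 |

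Repeat runs differ by about a point. At 9 df of noise the standard error rises from about 1.68 to 1.98.

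**5. Power under one-at-a-time entry.** One centred noise predictor with its treatment interaction leaves power at about 0.81.

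**6. False predictors.** One at a time, nine independent tests at 5%: 1 − 0.95^9 = 0.37. Jointly at 9 df, at least one false treatment-by-predictor interaction appears in about 32% of simulated trials.

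**7. Set comparison.** Neither way of entering the terms yields a contrast of the two sets. Raw in-sample fit would not supply one. With no true signal the expected R² is p/41: 4/41 = 0.10 for the clinical set and 5/41 = 0.12 for the neurological set at its leanest. The gap widens with each further imaging variable. For the joint 9-df model with treatment and interactions it is 19/41 = 0.46.

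**The case against.** The strongest defence is that the text does not force a single joint model. It speaks of models in the plural, never says that all predictors enter at once, and describes the treatment-by-time test before it mentions covariates. Treatment effect and prediction are given as two objectives. A lean test followed by separate predictor models fits that order, and step 5 shows that the AOT effect would then lose almost nothing. Useful predictors can also repay their cost: at 9 df with 30% of variance explained, power is about 0.80.

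Much of this stands, and it limits what can be claimed. A reader might infer any of the following, and the article does not support them:

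- **That the AOT effect is swamped.** This needs joint entry together with noise predictors or roughly 12 to 15 df or more.
- **That four lesion classes, and so 11 df, are the minimum.** The single global lesion score makes it 9.
- **That the treatment term is uninterpretable because covariates are uncentred.** The article does not address centring, a detail commonly left to an analysis plan.
- **That the second main objective has no analysis at all.** The interaction terms bear directly on the third and fourth hypotheses.

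The defence does not reach three points. The sentence states a rule, so it is not merely detail left to an unseen plan. It leaves open which model gives the confirmatory result. Its stated purpose is wrong on either reading, and one-at-a-time testing neither limits false predictors nor compares the two sets.

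**Conclusion.** The point holds in a conditional form. The covariate sentence does not separate the predictor models from the confirmatory AHA test, gives the wrong reason for the interactions, and provides no comparison that addresses the second hypothesis. These three conclusions do not depend on how the predictors are entered.

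The effect on power does. Under joint entry it ranges from almost none (0.80 at 9 df with 30% of variance explained) through a loss of about 17 points (0.65 at 9 df of noise) to about 0.4 to 0.5 at 15 df, with saturation at 20 df. Under one-at-a-time entry it is negligible, and the main cost is the roughly 37% chance of a false predictor.

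The figures assume complete data on 42 children, independent centred predictors and analysis of the T1-T2 change. The Transcranial magnetic stimulation section limits wiring assessment to eligible children without giving a number. If six lacked it (an assumption, leaving 36), power at 9 df of noise would be about 0.52. The sample size calculation itself is sound.

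**What to change.** In the Statistical analysis section:

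1. State that the confirmatory AHA result comes from a lean treatment-by-time model with pre-intervention AHA and the stratification factors (House class, age group, CST wiring).
2. Move the remaining predictors, and all predictor interactions, to a separate secondary analysis labelled exploratory, with one pre-named, centred summary per domain.
3. For the second hypothesis, fit clinical-only and neurological-only models in the same children and compare them by a cross-validated or otherwise optimism-corrected measure.
4. Replace the confounding rationale with prediction and effect modification.

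Cost: revised wording and some extra programming. The lean model is not free either. Its 5 df (AHA 1, House class 1, age group 1, wiring 2) give power of about 0.76 if they are pure noise and about 0.90 if they explain 30% of variance. Predictor results will be exploratory and imprecise with 42 children. One-domain-at-a-time tests remain open to false positives and the cross-validated comparison will be unstable, so both should be reported as such.

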## Discussion

This paper presents the background and design for a single-blinded RCT comparing mCIMT in combination with AOT to mCIMT alone in children with uCP and investigating the role of different neurological biomarkers in predicting treatment response. To the best of our knowledge, this is the first study to investigate the added value of a novel treatment approach based on a neurophysiological model (AOT) to a motor execution treatment model (mCIMT). The outcomes across all domains of the ICF will be evaluated using valid and reliable clinical tools as well as 3DMA. Furthermore, the predictive value of neurological factors on treatment response will be investigated. This may be useful in predicting which children respond best to these training approaches and thus assist in an effective allocation of resources.

The results of this study will be disseminated through peer-reviewed publications as well as active participations at international conferences. Participating in activities and events aimed at the translation of science will bring our research results to a broader audience (local clinicians, parents, and children).

## Abbreviations

3DFLAIR: Three dimensional fluid-attenuated inversion recovery
3DMA: Three dimensional movement analysis
AHA: Assisting Hand Assessment
AOT: Action-Observation Training
CC: Corpus callosum
CP: Cerebral Palsy
CST: Corticospinal tract
dMRI: Diffusion Magnetic Resonance Imaging
EMG: Electromyography
FOV: Field of view
HFC: House Functional Classification
HTH: Hand to head
HTM: Hand to mouth
HTS: Hand to shoulder
ICF: International Classification of Functioning, Disability and Health
JTHFT: Jebsen-Taylor hand function test
MA2: Melbourne Assessment 2
MACS: Manual Ability Classification system
mCIMT: Modified Constraint Induced Movement Therapy
MEPs: Motor-evoked potentials
MPRAGE: Magnetization prepared rapid gradient echo
MRI: Magnetic Resonance Imaging
pROM: Passive range of motion
RCT: Randomized controlled trial
RF: Reaching forward
RF: Reaching sideways
RGS: Reaching to grasp a sphere
RGV: Reaching to grasp a vertically oriented cylinder
RMT: Resting motor threshold
RS: Reaching sideways
rsfMRI: Resting state functional Magnetic Resonance Imaging
SPM: Statistical Parametric Mapping
TE: Echo time
TMS: Transcranial magnetic stimulation
TR: Repetition time
uCP: Unilateral cerebral palsy
UL: Upper limb
